## Abstract

**Background:**

The Portuguese National Health Directorate has issued clinical practice guidelines on prescription of anti-inflammatory drugs, acid suppressive therapy, and antiplatelets. However, their effectiveness in changing actual practice is unknown.

**Methods:**

The study will compare the effectiveness of educational outreach visits regarding the improvement of compliance with clinical guidelines in primary care against usual dissemination strategies. A cost-benefit analysis will also be conducted. We will carry out a parallel, open, superiority, randomized trial directed to primary care physicians. Physicians will be recruited and allocated at a cluster-level (primary care unit) by minimization. Data will be analyzed at the physician level. Primary care units will be eligible if they use electronic prescribing and have at least four physicians willing to participate. Physicians in intervention units will be offered individual educational outreach visits (one for each guideline) at their workplace during a six-month period. Physicians in the control group will be offered a single unrelated group training session. Primary outcomes will be the proportion of cyclooxygenase-2 inhibitors prescribed in the anti-inflammatory class, and the proportion of omeprazole in the proton pump inhibitors class at 18 months post-intervention. Prescription data will be collected from the regional pharmacy claims database. We estimated a sample size of 110 physicians in each group, corresponding to 19 clusters with a mean size of 6 physicians. Outcome collection and data analysis will be blinded to allocation, but due to the nature of the intervention, physicians and detailers cannot be blinded.

**Discussion:**

This trial will attempt to address unresolved issues in the literature, namely, long term persistence of effect, the importance of sequential visits in an outreach program, and cost issues. If successful, this trial may be the cornerstone for deploying large scale educational outreach programs within the Portuguese National Health Service.

**Trial registration:**

ClinicalTrials.gov number NCT01984034.

## Background

Patients often do not receive treatment that is supported by best evidence. This includes both failure to provide treatment proven to be cost-effective and provision of care that is unnecessary or harmful [1]. High quality clinical guidelines synthesize the current best knowledge, make transparent recommendations for current best practice, and can improve the quality of care [2]. However, it is recognized that guidelines alone are insufficient to change clinical practice and that implementation strategies are required [3-5].

There is a wide range of such strategies but limited evidence to assess their comparative effectiveness, as there are few head-to-head trials. Some overviews of systematic reviews provide narrative synthesis of the evidence supporting the different interventions [1,4,6,7]. However, primary studies are too diverse and heterogeneous to allow for more robust methods of indirect comparison. The Cochrane Collaboration Effective Practice and Organization of Care Group has assessed several strategies through high quality systematic reviews. Printed educational materials have no apparent effect on processes of care, while educational meetings, educational outreach, local opinion leaders, audit and feedback, computerized reminders, and tailored interventions are associated with small but clinically significant improvements [8-14].

Educational outreach interventions are personal visits by a trained individual (hereafter named as detailer) to health professionals in their own settings [10]. This detailer is usually a healthcare professional (physician, nurse or pharmacist) with special training in communication skills. He or she presents educational contents prepared by an independent organization (such as a university) to an individual physician. The Cochrane Review estimates a small but consistent effect on prescription improvement (median 4.8%, interquartile range 3.0% to 6.5%) [10].

### Local context

In Portugal, healthcare is provided by two overlapping systems: a publicly funded National Health Service (NHS), and voluntary private and public health insurance. The NHS has universal coverage, and 20% of the population has additional insurance coverage [15]. Thus, most primary care is provided by the NHS.

NHS Primary care physicians work in units typically with 4 to 12 doctors, along with nurses and secretaries. On average, each family physician cares for about 1,700 patients. The NHS distinguishes two types of primary care units. The default one is the ‘personalized care units’ model, in which professionals receive a fixed salary. The other model is the ‘family health units’, which enjoy greater functional and organizational autonomy [16]. ‘Family health units’ start as type-A units, in which professionals receive a fixed salary as in the former model. If these A units meet quality indicators targets, they become type-B units, in which health professionals have a mixed payment scheme that includes salary, capitation, and pay for performance.

Within this context, prescription drugs have a variable patient co-payment, depending on their therapeutic value [15]. Electronic prescribing has been mandatory for all NHS reimbursed drugs since 2012. All prescription information is collected centrally by NHS [17].

National prescribing guidelines are commissioned by the National Health Directorate (a government agency) to academic researchers and key opinion leaders. This agency also monitors the quality indicators set in each of its guidelines [18,19]. These guidelines are published in the agency’s website (http://www.dgs.pt). Health professionals are expected to visit this website regularly to keep up-to-date with the latest guidelines. Therefore, this study will not have a group of naive physicians unexposed to guidelines. For this reason, the control group is composed of physicians exposed to passive guideline dissemination (the usual implementation strategy).

### Choice of design

The design is a parallel, open, cluster, superiority randomized trial with a 1:1 allocation ratio. This study will assess the effect of educational outreach visits on physician compliance with prescription guidelines. Although the intervention is targeted at individual physicians, there is a risk of contamination if the randomization occurs at the individual level. This is because physicians in the same practice might be influenced by intervention subjects (*e.g.*, by raising awareness of the topics, through discussion of difficult patient cases, or by sharing visit content). Therefore, a cluster-randomized design is appropriate. Also, the costs (*e.g.*, travel expenses, salary costs of the detailers) in a cluster-randomized design will better approach the real costs of this intervention if implemented as a public health program. Therefore, to minimize contamination and for practical reasons, the unit of allocation will be the primary care unit. The unit of analysis will be the family physician.

### Aim and objectives

This trial aims to assess whether educational outreach visits are superior to usual implementation of guidelines regarding the reduction of inappropriate prescribing. The primary outcomes will be the long-term (18 months) effects in the prescription of cyclooxygenase-2 (COX-2) inhibitors, and omeprazole, by family physicians. The secondary outcomes will be the short (1 month) and medium-term (6 months) effects of educational outreach visits in the prescription of these two drug classes. Other secondary endpoints will be the short, medium and long-term effects of educational outreach visits in the prescription of clopidogrel. Finally, the trial will determine the cost-benefit of educational outreach visits.

## Methods

The study will be a parallel, cluster-randomized controlled trial comparing educational outreach visits with usual guideline implementation. Besides the standard description below, we also provide a summary of the intervention, a PaT plot, and a cascade diagram in Additional file 1[20,21]. This protocol was written in accordance with the Consolidated Standards of Reporting Trials (CONSORT) statement - Additional file 2.

### Participants and setting

The trial will recruit family physicians employed in primary care units of the National Health Service of the Lisbon region, Portugal. This region comprises over 3.5 million patients. A primary care unit (the cluster) will be eligible if it has at least four family physicians (which represent about 6,800 patients). Physicians that are planning to retire within two years, and those without an assigned or still building (far from the average number of patients) patient list will be excluded. At least four family physicians in each unit have to be willing to participate in order for the unit to be included in the trial.

The expected participant flow is described in Figure 1. The research authors will meet with the coordinators of each unit, briefly explaining the protocol and extending them an invitation to participate. The coordinators will be asked to share trial information with other physicians in their units. The researchers will then contact and screen willing primary care units until the target number is met. The enrollment period will last six months. There will be no financial incentive for participation.

**Figure 1 F1:**
[figure not shown]
Flow of participants.

Baseline data will be collected from the primary care units (number of family physicians, type of primary care unit, urban versus rural setting, baseline prescription of COX-2 inhibitors, baseline prescription of omeprazole) and from the family physicians (age, gender, number of years of practice after vocational training, currently training residents). Participating physicians will agree to schedule three educational outreach visits, one for each guideline.

### Allocation to intervention and blinding

Clusters will be enrolled and allocated randomly. To achieve a good balance regarding baseline characteristics that can influence the outcome, the allocation sequence will be determined by minimization [22]. This stratified randomization method will balance the control and intervention groups for number of physicians (4 or 5, 6 or 7, 8 to 12), median baseline prescription of COX-2 inhibitors (above or below the regional median), median baseline prescription of omeprazole (above or below the regional median), proportion of physicians with fewer than 10 years of practice after completing vocational training (above or below 50%), and type of primary care unit (family health unit or personalized care unit). All physicians sending the consent statement before the cluster allocation will be included in the study.

The sequence of intervention visits for each unit will be determined by simple randomization.

Allocation concealment will be ensured by the following procedures: the trial manager (hired and not part of the authors research team) will assign a sequential number to each unit as participation forms are received; only anonymized data about participating units will be sent to the trial statistician (sequential number and minimization variables); data will be sent in two batches, one for each half of all units; the sequence of visits will be determined using the random sequence generator from Random.org (http://www.random.org/sequences/); the statistician will blindly allocate units to each trial arm using minimization and return allocation information to the trial manager.

Due to the nature of the intervention, neither family physicians nor detailers can be blinded. Outcomes are routinely collected by the regional health administration independently of the researchers or the trial and will only be sent to researchers after the intervention has ended. Upon receiving prescription data, the trial manager will generate a random code (using http://www.randomcodegenerator.com) to designate intervention and control units and another code for the order of the visits. Data analysts (the trial statistician plus one of the members of the research team) will receive a file with these codes, ensuring they will be blinded to group and visit sequence allocation until all analyses are completed.

### Intervention and comparison

Physicians in units randomized to the intervention will have three educational outreach visits during a six-month period. These visits will promote the implementation of governmental guidelines on the prescription of the following agents: non-steroidal anti-inflammatory drugs (NSAIDs) and COX-2 inhibitors, acid secretion modifiers, and antiplatelets [23-25]. The outcomes for the trial were chosen according to the main key-message from each guideline. For NSAIDs, COX-2 inhibitors should be prescribed only in patients with increased gastrointestinal risk who do not tolerate a classic NSAID associated with a gastroprotective agent; for acid secretion modifiers, all proton pump inhibitors are equivalent in effectiveness, so omeprazole should be used in most patients as it is the least expensive; for antiplatelets, there is no benefit of maintaining long term clopidogrel after a myocardial infarction, acute coronary syndrome, or percutaneous coronary intervention.

During each 15- to 20-minute visit, an academic detailer will promote one of the guidelines to a family doctor (up to three physicians may be present in each visit if they wish to, but one-to-one visits will be preferred and encouraged). The detailer will also distribute a point of care summary highlighting the main messages. The team of academic detailers will be as following: three members of the steering committee (two family physicians and one academic pharmacologist), three family physicians, and nine family medicine residents in the fourth and final year of their specialty training. The three members of the steering committee completed training in the methodology of academic detailing with the National Resource Center for Academic Detailing (Boston, MA). The other 12 detailers were trained locally by this steering committee, with pre-training study assignments, and 12 hours of face-to-face training that included the principles of academic detailing, role-playing, video-recording and feedback, discussion of the scientific content of each guideline, and knowledge assessment. To ensure consistency, the contents of each visit (structure, guideline features to highlight, and written materials) have been prepared in advance by the steering committee and were used in the training sessions. Whenever possible, a single detailer will perform all three visits to the same physician. The definition and methodology of educational outreach visits has been published elsewhere [10,26].

Usual guideline implementation consists of passive dissemination by their publication on the National Health Directorate’s website. Physicians in units randomized to the control group will be offered an unrelated training session (coding with the International Classification of Primary Care, second edition) as a token of good will for participating in the trial.

This trial has a pragmatic purpose. To improve adherence to the educational outreach visits, the Regional Health Administration will allow family physicians to use a patient visit slot (15 to 20 minutes) for each of the three visits, but physicians may also choose to have the visit before or after their regular hours. The first visit will be scheduled by the trial manager contacting the target family physician. Subsequent visits will be scheduled directly between the detailer and the target family physician. Also to improve adherence, participating physicians will be asked to allow us to use their personal phone numbers and emails. We will use these to send them a reminder of the visit two days before it is scheduled. Rescheduling the visit will be allowed up to the day before it is scheduled to take place; if the physician is unable to attend the visit but cannot warn the detailer beforehand, no additional efforts will be made to reschedule that visit (*i.e.*, the program will continue with the next guideline). The intervention will be discontinued at physician request or if the physician changes workplace. Participating physicians will not be prohibited from receiving any other interventions during the trial.

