#### Timing of outcome collection

Unlike a randomized controlled trial for a drug, we do not expect the intervention to be delivered immediately after allocation. This is because there are a limited number of detailers, and their time for visits is also limited (as they themselves are practicing physicians). Plus, family physicians’ availability to receive visits from these detailers is also constrained by their heavy workload. These constraints will prevent us from delivering the intervention to all physicians in a short period (*e.g.*, less than one month). We plan to deliver the full intervention to all physicians in the experimental group over a period of six months. For each guideline, we will seek to visit all the physicians belonging to the same cluster in the shortest time possible, to limit contamination within clusters. This will cause the gap between allocation and intervention dates to vary depending on the participating unit. Thus, if we assess the outcome at a fixed time following randomization, participating units will have different follow-up times after the intervention, and as a result the observed intervention effect will be unreliable. Moreover, since we will have three visits for each physician, there will also be differences in the time of intervention between guidelines. For these reasons, outcomes will be measured from specific intervention dates rather than from the general allocation date. This will provide more reliable data about the efficacy of the intervention.

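### Units where a detailer works are neither excluded nor balanced, so a control unit can have a trained detailer on its staff

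*Protocol article*

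**What the plan says.** The Choice of design section justifies allocation by unit on the ground that "physicians in the same practice might be influenced by intervention subjects", for example through talk about cases or about what was said in a visit.

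Intervention and comparison lists the detailers as "three members of the steering committee (two family physicians and one academic pharmacologist), three family physicians, and nine family medicine residents". That is five family physicians, nine final-year residents and one pharmacologist. The same section adds that "The other 12 detailers were trained locally by this steering committee", with 12 hours of face-to-face training that covered the content of each guideline. Timing of outcome collection explains that detailers' time is limited "as they themselves are practicing physicians".

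Participants and setting gives the unit criterion: "A primary care unit (the cluster) will be eligible if it has at least four family physicians". The physician exclusions begin "Physicians that are planning to retire within two years, and those without an assigned or still building" and concern retirement and the patient list only. Detailers and their workplaces do not appear. The baseline physician data include "number of years of practice after vocational training, currently training residents", so residents are expected in at least some recruited units.

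Under Allocation to intervention and blinding, the minimisation factors are number of physicians, two baseline prescribing measures, years of practice, "and type of primary care unit (family health unit or personalized care unit". The statistician receives only a sequence number and these variables. Every physician who consents before the cluster is allocated is included.

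**The concern.** The design guards against a visited physician passing the message to an unvisited colleague. The same reasoning applies at least as strongly to a colleague who has been trained to deliver that message. As written, the plan allows such a colleague to work in a control unit, and the allocation step cannot take account of it because the information never reaches the statistician. Nor would the exposure be seen later, since the detailers' records described under Data collection concern the planned visits.

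Two things are at stake. A detailer in a control unit would pull the comparison toward no effect. A detailer in an intervention unit would add exposure beyond the three visits, so any bias need not run in one direction only. A family-physician detailer who enrolled would also contribute his or her own prescribing to one of the arms.

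**Working it through.** **Inputs from the protocol article.** Sample size section: difference 5 points; COX-2 SD 7.4 and ICC 0.249; omeprazole SD 10.1 and ICC 0.027; six physicians per unit; alpha 0.025; 80% power; dropout 15%; 110 physicians per group; 38 units, so 19 per arm. Participants and setting: over 3.5 million patients in the region. Local context: about 1,700 patients per physician.

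**Reproducing the stated sample size.** n per group = 2 × [SD × (z₀.₉₈₇₅ + z₀.₈₀)/5]² × [1 + (6 − 1) × ICC] / 0.85.

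- COX-2: 41.64 × 2.245 = 93.5; 93.5/0.85 = 110. This matches the article (112 if rounded up at each step).
- Omeprazole: 77.57 × 1.135 = 88.0; 88.0/0.85 = 104.

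COX-2 therefore sets the sample size, and it has no reserve above 80%. Alpha of 0.025 must be two-sided to reach 110; a one-sided 0.025 gives about 91 to 93.

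**How many detailers to expect in control units.** Assumptions: the 14 family medicine detailers all work in units of the region, independently of each other, and recruitment is unrelated to where they work. Six to eight physicians per unit is also assumed.

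- Physicians in the region: 3,500,000/1,700 ≈ 2,060.
- Units: 2,060/8 ≈ 257 to 2,060/6 ≈ 343.
- Share of units that are controls: 19/343 = 5.5% to 19/257 = 7.4%.
- Expected detailers in control units: 14 × 0.055 ≈ 0.8 to 14 × 0.074 ≈ 1.0.
- Chance of at least one: 1 − (1 − 0.055)¹⁴ ≈ 55% to 1 − (1 − 0.074)¹⁴ ≈ 66%.

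**Effect on power.** Let k be the number of control units with a detailer on staff and f the share of the effect that reaches them. Neither is in the article, so a range is shown.

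- Diluted difference: d = 5 × (1 − f × k/19).
- Power = Φ(d/SE − z₀.₉₈₇₅), with SE = SD × √(2 × design effect/93.5), where 93.5 = 110 × 0.85.
- Undiluted (k = 0): 80.0% for COX-2 and 82.5% for omeprazole.

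| k | f | difference (points) | COX-2 power | omeprazole power |
|---|---|---|---|---|
| 1 | 0.25 | 4.93 | 78.9% | 81.4% |
| 1 | 0.5 | 4.87 | 77.7% | 80.3% |
| 1 | 1 | 4.74 | 75.2% | 77.9% |
| 2 | 0.25 | 4.87 | 77.7% | 80.3% |
| 2 | 0.5 | 4.74 | 75.2% | 77.9% |
| 2 | 1 | 4.47 | 69.8% | 72.6% |
| 4 | 0.25 | 4.74 | 75.2% | 77.9% |
| 4 | 0.5 | 4.47 | 69.8% | 72.6% |
| 4 | 1 | 3.95 | 57.6% | 60.5% |

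The rows for k = 1 correspond to the expected count above. Those for k = 2 and 4 show what happens if recruitment happens to favour units where detailers work. The table counts leakage in the control arm only. Extra exposure in intervention units would offset part of the power loss, but through an effect that the three visits did not produce.

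**The case against.** The strongest reply is that this argues from silence. No two sections contradict each other, the article never says where a detailer works, and a condensed article may leave such arrangements to the full protocol. The point about workplaces stands and limits what can be claimed. The point about silence carries less weight: the article sets out its unit criteria, physician exclusions and minimisation factors in detail, and none of them deals with detailers.

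Several stronger readings are tempting, and the text does not support them:

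- A reader might infer that the comparison is contaminated. The article shows only that it can be.
- That 12 detailers were trained locally might be taken to show that they are employed in the region. The phrase contrasts with the steering committee's training in Boston and says where training took place.
- All 14 clinicians might be thought able to enrol. The nine residents are unlikely to have an established patient list and so are probably excluded already; at most the five family physicians are in question.
- Control physicians might be pictured beside a detailer for all 18 months. Final-year residents may have left the unit before then.
- Recruitment might be read as running through the authors' personal networks. The article says only that they will meet unit coordinators and then screen willing units.

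It is also fair to say that random allocation balances such units between arms in expectation, so their absence from the minimisation factors is not in itself a defect. With 19 units per arm and about one affected control unit expected, however, balance in expectation does not keep detailers out of control units.

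**Conclusion.** The concern holds in a limited form. The plan as written permits a trained detailer on the staff of a control unit, and the enrolment of a family-physician detailer, against its own reason for randomising by unit. Whether either would occur cannot be told from the article.

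The likely size is modest. Under the stated assumptions about one control unit would be affected, which costs about 1 to 5 percentage points of COX-2 power and shrinks a 5-point difference by 0.07 to 0.26 points. There is also a 34 to 45% chance that no control unit is affected. Several affected units would matter more, but nothing in the article shows that to be likely. The case for acting rests on how easily the risk is removed rather than on its expected size.

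**What to change.** Add to Participants and setting that a unit where any detailer or steering-committee physician works or trains is not eligible, and that detailers cannot be participants. Do this before any unit is allocated; the Trial status section reports that none had been randomised at submission. If such a unit has already agreed to join, replace it before allocation.

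If a unit of this kind must be kept, record detailer presence before allocation and pre-specify a sensitivity analysis without those units.

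The cost is at most about 14 of roughly 257 to 343 candidate units (about 4 to 5%), possibly including some of the more willing ones. The target of 110 physicians per group in 38 units is unchanged. A residual limit is that a resident could move into a trial unit after qualifying, which an exclusion at enrolment does not prevent.
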